### 3.10. Control Group

Mothers in the control group will be encouraged to spend the same amount of time next to the incubator, observing the infant’s behaviours through a standard cluster of indicators. It’s important that mothers in the control group are sustained in the presence and in the observation tasks, in order to minimize the negative effects of separation in the NICU.

## 4. Measures

### 4.1. Baseline Measures

#### 4.1.1. Infant’s Measures

As a physiological assessment, electrocardiogram (ECG) recordings will be collected during a 20-min baseline period, in the absence of the mothers, at the same hour as that of the intervention. We will also use a qualitative assessment of general movements (GMs) to assess behaviour. A video of the baby’s general movements will be collected in the baseline period. The video coding will be performed on blinded videos by two independent researchers.

#### 4.1.2. Maternal Measures

Baseline demographic data will be collected from the digital recorded data for each patient. In addition, a socio-economic status questionnaire will be administered to each participant and the Socio Economical Score (SES) will be calculated. To determine baseline stress, the Parental Stressor Scale (PSS-NICU) questionnaire will be administered to the mothers before intervention (T0) and before discharge, both in the intervention and control groups. The PSS-NICU [71,72] aims at assessing the parental perception of stressors derived from the physical and psycho-social environment of the NICU across three domains: their parental role, their infant’s behaviour and appearance, and the sights and sounds in the NICU. For each domain, a mean score will be assessed, and a final composite stress score will be calculated from the mean values of the single scores. Each mother, at each time point, will receive a final score for the single questionnaire (range 0–10). 

A questionnaire on musical experience [73] will be administered at T0. The questionnaire gives three scores for musical expertise, musical habits in everyday life, and music as an emotional experience. 

#### 4.1.3. Environmental Measures

In each centre, the background noise levels will be acquired via a calibrated sound level meter (Voltcraft Phonometer SL-10; Conrad Electronic, Hirschau, Germany) in the room where the intervention will take place and inside the incubator, 10 cm from the newborns’ head. This measure will be assessed at every intervention session to ensure that the mother’s voice is audible to the newborn (i.e., it exceeds the background noise of 10 dBA). No further analyses will be performed on these values.

## 5. Outcome Measures

### 5.1. Primary Outcome Measure

#### Physiological Level

During the interventions, time and frequency analysis of HRV will be applied to the following parameters: LFpower (power in the LF band), HFpower (power in the HF band), LFnu (normalised power in the LF band [LF power/(LFpower + HFpower)]); HFnu (normalised power in the HF band [HF power/(LFpower + HFpower)]); LF% (percentage power in the LF band [LF power/total power]), HF% (percentage power in the HF band [HF power/total power]), and LF/HF (ratio between LF power and HF power). The change from baseline will be calculated across the three conditions (i.e., singing, speaking, and control).

HRV will be measured through the acquisition of the ECG signal, via electrodes placed on the infant’s chest by routine medical devices. Subsequently, the ECG signal will automatically be recorded by the IxTrend Software (Ixellence GmbH, Wildau, Germany). Moreover, the heart rate (beats per minute), oxygen saturation (%), and all critical events (hypoxemia, oxygen saturation <80%; bradycardia, heart rate <80 bpm) will be acquired during the different conditions using the relevant medical apparatus. 

The physiological level is strictly dependent on the infant’s behavioural state (i.e., quiet, active, indeterminate, awake, or crying), which will be assessed offline from the video-recorded sessions by blinded coders, according to the Prechtl scale [8]. Measures of physiological parameters will be collected over the intervention period, as well as 20 min before and after the mother’s intervention.

### 5.2. Secondary Outcome Measures

Secondary outcome measures are presented in Figure 1.

#### 5.2.1. Infant’s Measures

Neurobehaviourally, GMs [8] will be measured at T0 and T1 (at term equivalent age) in both groups. Infants will be reassessed at 3 months. The GMs quality from video recording will be scored according to the Ferrari optimality score [74]. Two blinded coders will attribute a single final score for each infant at each time point. Inter-rater reliability will be assessed, and the mean scores will be compared between the intervention and control groups at each time point.

Developmental Level: Developmentally, the Griffiths Mental Development Scales (GMDS) [75] and a routine neurological examination (EON) will be administered to infants by trained researchers at 6 (T2), 12 (T3), and 24 (T4) months CA. 

These GMDS assess infant development across five main areas (locomotor, personal and social skills, hearing and language, eye and hand coordination, and performance), providing a general developmental quotient (DQ) of infant’s abilities and five sub-scale quotients (SQ).

The EON will be assessed with a final positive or negative score. In case of a negative score, the infant will be excluded from further analyses. The Italian version of the MacArthur–Bates Communicative Development Inventory [76,77] will be completed by parents at 12 (Gestures and Words Form) and 24 (Words and Sentences Form) months CA. Furthermore, the expressive and receptive language test, Parole in Gioco [78], will be administered to infants by trained researchers at 24 months. Each child, at each time point, will receive a final score for each questionnaire, measured as a discrete numeric value. 

Next, an audiological evaluation using an auditory brain system response will be performed within 3 months of CA and repeated at 12 and 24 months with behavioural audiometry techniques. A positive or negative evaluation will be obtained. In the case of negative audiological evaluation, the infant will be excluded from analyses.

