### 3.7. Sample Size and Power Analysis

The main outcome measures for the primary outcome will be the low-frequency (LF) and high-frequency (HF) power of the HRV measure. We expect the baseline measurement mean value (±standard deviation) of LF and HF power for preterm infants to be 31 ± 4.9 Hz and 15 ± 2.6 Hz, respectively [58]. We assume that the treatment in the experimental population is effective if the mean values of LF and HF power reach 25 ± 4.9 and 17 ± 2.4 Hz, respectively. 

With an alpha setting at 0.025 and beta setting at 0.80, it is necessary to enroll 29 patients per group. Assuming a 20% loss, we aim to enroll at least 80 patients total (40 per group).

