### 3.8. Randomisation

A centralised patient randomisation will be performed using a secure, web-based randomisation system, through which the study investigator of each centre can register new patients and obtain the treatment arm assignment.

A block allocation sequence with variable block sizes (block size 2–4), stratified by GA and gender, will be generated using Stata statistical software (StataCorp, College Station, TX, USA) with the “ralloc” command. In case of twins, randomisation will be conducted at the level of the family (i.e., twins will be randomised to the same group). The allocation sequence will be concealed from the investigators.

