### 8.2. Secondary Outcomes

To assess the effect of EVC on the neurobehavioral and developmental outcomes of newborns, as well as on maternal stress and presence in the NICU, the values for the different scales and questionnaires will be compared (at the time points specified in the Secondary Outcome Measures) between the intervention and control groups. Confounding variables will be entered in the analysis (i.e., familiar socio-economical score, gestational age at birth) to partial out any effect which they could have on the difference between the outcome measures. For continuous variables the Wilcoxon-Mann-Whitney test will be applied, while for categorical variables the chi-squared test (or Fisher’s exact test where appropriate) will be applied. 

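### The general-movement score is measured before the intervention, but the later between-arm comparisons do not use that value; precision is lost on a secondary outcome, without bias

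*Protocol article*

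**What the plan says.** All places are in the protocol article.

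- **Baseline.** Section 4.1.1: "A video of the baby’s general movements will be collected in the baseline period". Section 5.2.1: "GMs [8] will be measured at T0 and T1 (at term equivalent age) in both groups", with a further assessment at 3 months.
- **Comparison.** Section 5.2.1: "the mean scores will be compared between the intervention and control groups at each time point". Section 8.2 applies the same between-group comparison to all secondary scales at their specified times.
- **Covariates.** Section 8.2: "Confounding variables will be entered in the analysis (i.e., familiar socio-economical score, gestational age at birth". No T0 score and no gender.
- **Test.** Section 8.2: "For continuous variables the Wilcoxon-Mann-Whitney test will be applied".
- **Randomisation.** Section 3.8: the sequence is "stratified by GA and gender".

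A baseline value is used for other measures: section 5.1 calculates change from baseline for heart rate variability, and section 5.2.2 compares maternal stress before and after. No section does either for general movements, and gender appears in no stated analysis.

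**The concern.** The general-movement score carries the neurobehavioural hypothesis in section 2. When an outcome has been measured before treatment, its baseline value is often among its best predictors, and conditioning on it removes outcome variation that has nothing to do with treatment. The stated analysis leaves that variation in. The sample was sized on heart rate variability (section 3.7), so nothing guarantees adequate power for this score, and precision already paid for is worth keeping.

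Two related points sit in the same text. Gender was used to stratify the randomisation but is absent from the analysis. And section 8.2 promises covariates while naming a test that, in its standard form, cannot carry any, so even the listed covariates have no stated route into the analysis.

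**Working it through.** **The plan's own figure.** Section 3.7 states "With an alpha setting at 0.025 and beta setting at 0.80, it is necessary to enroll 29 patients per group". I read 0.80 as power. The article does not say whether alpha is one- or two-sided.

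- HF power: difference 17 − 15 = 2; pooled SD = √((2.6² + 2.4²)/2) = 2.50.
- n = 2 × [2.50 × (z₀.₉₈₇₅ + z₀.₈₀)/2]² = 29.75, so 30 per group with two-sided alpha 0.025. At 29 per group, power is 0.789.
- LF power: difference 6, SD 4.9, giving 13 per group, so HF drives the size.
- A one-sided 0.025 gives 25 for HF and does not match.

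The stated 29 is therefore reproduced to within one infant per group. It concerns the primary outcome only; the article gives no sample size for general movements.

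**Infants available.** 40 per group with 20% loss leaves 40 × 0.80 = 32 per arm.

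**Effect of using the T0 score.** Let ρ be the partial correlation of the T0 score with the later score, given the other covariates. Adjustment multiplies the variance of the arm difference by 1 − ρ² and its standard error by √(1 − ρ²). Effective n per arm is 32/(1 − ρ²). The smallest difference detectable with 80% power, in SDs of the score before T0 is added, is

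(z₀.₉₇₅ + z₀.₈₀) × √(2/32) × √(1 − ρ²) = 0.70 × √(1 − ρ²).

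The values of ρ, the two-sided 5% level and the 0.5 SD effect in the last column are assumptions; none is in the article.

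| ρ | Variance factor | SE factor | Effective n per arm | Detectable difference (SD) | Power for 0.5 SD |
|---|---|---|---|---|---|
| T0 not used | 1 | 1 | 32 | 0.70 | 51.6% |
| 0.3 | 0.91 | 0.954 | 35.2 | 0.67 | 55.4% |
| 0.5 | 0.75 | 0.866 | 42.7 | 0.61 | 63.7% |
| 0.7 | 0.51 | 0.714 | 62.7 | 0.50 | 80.0% |

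**Allowing for gestational age.** Section 8.2 already intends to adjust for it, so a marginal correlation overstates the gain. Take a marginal correlation of 0.5, with gestational age correlated 0.3 with each score (assumed):

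partial ρ = (0.5 − 0.3 × 0.3)/√((1 − 0.3²)(1 − 0.3²)) = 0.41/0.91 = 0.45,

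and 1 − 0.45² = 0.80. The reduction is about 20% rather than 25%.

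**Chance imbalance at T0.** The T0 difference between arms has standard error √(2/32) = 0.25 SD, so an imbalance of at least 0.25 SD in either direction arises in about 32% of such trials. At a correlation of 0.5 it shifts the later difference by 0.5 × 0.25 = 0.125 SD. Only that fraction carries over.

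**Gender.** If gender explains 1% to 5% of the variance (assumed), the standard error is multiplied by √0.99 = 0.995 to √0.95 = 0.975, and power for 0.5 SD moves from 51.6% to between 52.0% and 53.7%.

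**The case against.** The strongest reply is that nothing here is invalid. Under randomisation, a comparison at T1 or 3 months that ignores T0 is unbiased. **That stands.** A reader might infer that the planned comparison is biased, or that any T0 imbalance passes in full into later scores. The article supports neither: imbalance averages to zero over randomisations and carries over only in proportion to the correlation.

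A reader might also infer that the scores are compared with no adjustment at all. Section 8.2 does intend covariates, including gestational age, the other stratum. The accurate statement is that the T0 score and gender are not among those named.

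The covariate list may not be closed. It is introduced by *i.e.*, which section 1.2 uses loosely for what look like examples. So the omission is what the text states, not proof that the investigators would refuse other covariates. Nor is a significance test at T0 certain: section 5.2.1 speaks only of comparing means, and a descriptive comparison at T0 would fit.

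The correlation is unknown and could be low. Under section 3.9 the intervention starts once criteria are met, so T0 falls at varying maturity, whereas T1 and 3 months are fixed ages. Below 0.3 the standard error improves by less than 5%. This limits the claim about size, not its direction.

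Finally, a covariate set could be left to an analysis plan that is not shown. But the article is not silent: it states the comparison, the covariates and the test, and the last two do not fit together.

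**Conclusion.** The point holds as a loss of precision on a secondary outcome, not as a bias. The T0 general-movement score is collected and not used in the stated comparisons at T1 and 3 months.

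The size cannot be derived from the article. It rests on an assumed partial correlation: variance falls by about 9%, 25% or 51% at 0.3, 0.5 or 0.7, and less where gestational age already accounts for part of the T0 score. The direction holds for any non-zero partial correlation, apart from the small cost in degrees of freedom.

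Leaving out gender costs little precision. The case for including it is mainly that the analysis should match the stratified randomisation. The mismatch between promised covariates and a test that takes none needs correcting whatever the correlation.

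**What to change.** 1. **General movements (sections 5.2.1 and 8.2).** Analyse the T1 and 3-month scores by analysis of covariance, rank-based if the scores are skewed, on arm, T0 score, gestational age, gender and the already planned socio-economic score. Report T0 scores by arm descriptively only.
2. **Other continuous infant outcomes (section 8.2).** Replace the Wilcoxon-Mann-Whitney test by a model that can carry covariates, with gestational age, gender and socio-economic score. The developmental and language scales have no T0 value, so the change there is the model and the addition of gender.

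**Cost.** Wording only; every variable is already collected. With 64 evaluable infants and one term per covariate, adding T0 score and gender takes the residual degrees of freedom from 64 − 4 = 60 to 64 − 6 = 58. If the partial correlation is near zero, that is spent for no gain. The plan must also say how an infant with a missing T0 score is handled, so that the adjustment does not drop infants from the comparison.

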### 3.3. Participants

Eighty preterm infants, born at 25–32 weeks and 6 days GA, will be recruited from the four centres (20 per centre). Recruitment will be undertaken in each centre by a trained research assistant (RA), who will review birth records daily. After obtaining permission from the attending physicians of both the mother and infant, the RA will invite qualifying families to participate and will obtain written informed consent from those enrolling. Infants will be then assigned to the EVC intervention or control group using a randomised design, stratifying infants by gender and GA (see Randomisation). Mothers whose infants are assigned to the control group will be asked to spend the same amount of time as that of mothers in the intervention group, observing their infants’ spontaneous behaviour, with the subsequent compilation of an observation grid developed ad hoc, according to few indicators drawn from The Neonatal Behavioural Assessment Scale. The mothers whose infants are assigned to the control group will be asked not to vocally interact with them during the observational intervention.

Recording sessions will take place midway between the feeding cycles, more than 1 h after the feed and more than 4 h after the last medical exam.

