### 3.6. Exclusion Criteria

The exclusion criteria for the newborns will be: PVL grade III and IV, IVH grade III and IV, sepsis (vertical and horizontal), congenital malformations and/or genetic abnormalities, requiring respiratory support with high flow/nCPAP repeated apnoea associated with bradycardia and fall of saturation, hyaline membrane disease, respiratory distress syndrome, and hyperbilirubinaemia requiring exchange transfusions during hospitalisation. 

Lack of informed consent will exclude the infant from the study.

The exclusion criteria for the mothers will be presence of depressive symptoms, drug abuse, and age below 18 years.

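### Infants with a negative neurological or hearing result after randomisation are removed from analysis, so the developmental comparison rests on a post-randomisation subset

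*Protocol article*

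**What the plan says.** Section 5.2.1 of the protocol article, under Secondary Outcome Measures, contains two analysis rules.

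- **Neurological examination.** EON and the Griffiths scales are "administered to infants by trained researchers at 6 (T2), 12 (T3), and 24 (T4) months CA". "The EON will be assessed with a final positive or negative score". The rule follows: "In case of a negative score, the infant will be excluded from further analyses".
- **Hearing.** The evaluation is "performed within 3 months of CA and repeated at 12 and 24 months with behavioural audiometry techniques". The rule is: "In the case of negative audiological evaluation, the infant will be excluded from analyses".

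Allocation comes well before either test. Section 3.3 says, of the step after consent: "Infants will be then assigned to the EVC intervention or control group using a randomised design". Section 3.9 has the intervention start soon after birth and run for two weeks in hospital.

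The Griffiths areas are "locomotor, personal and social skills, hearing and language, eye and hand coordination, and performance". MacArthur–Bates is completed at 12 and 24 months, and Parole in Gioco at 24 months. Section 8.2 compares the arms on these scales and names socio-economic score and gestational age at birth as the variables to adjust for. The article names no analysis that keeps the excluded infants.

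**The concern.** Randomisation makes the arms comparable as allocated. A filter applied months later keeps them comparable only if allocation has no bearing on who passes it. Here the filter is a pair of tests that the plan itself lists as outcomes. One of them sits under the developmental heading beside the Griffiths scales, which themselves score motor, hearing and language ability.

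Section 2 expects EVC to have a direct effect on cognitive and linguistic development. If EVC also lowers the chance of a negative examination, some infants it helped stay in the EVC arm while comparable control infants are removed. The control mean rises more than the EVC mean, and the benefit shrinks. If EVC did harm, the same mechanism would remove more EVC infants and hide part of it. Adjusting for baseline variables does not repair selection that happens after treatment.

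At stake are the long-term developmental comparisons, one of the stated aims, in a trial of only 40 infants per arm.

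**Working it through.** **What the document supplies.** It gives no rate of negative EON or audiology results, no Griffiths SD and no correlation between the tests and the scales. There is no plan figure to reproduce on this point, and the bias cannot be computed from the document. What follows is an illustration.

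**Order of events.** Allocation in the NICU, then two weeks of intervention. Hearing is tested within 3 months corrected age and again at 12 and 24 months; EON is done at 6, 12 and 24 months. Every test that can trigger removal follows both allocation and treatment.

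**Assumed inputs.** Griffiths SD 15. True benefit 5 points, so d = 5/15 = 0.333. A latent EON score with unit variance, correlated r = 0.6 or 0.8 with the Griffiths score. A cut-off c below which a proportion q of controls is negative, with q = 3%, 5% or 15%. EVC moves the latent EON score by s.

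**Formula.** Let λ(x) = φ(x)/(1 − Φ(x)). Retaining only infants above the cut-off raises the control mean by 15·r·λ(c) and the EVC mean by 15·r·λ(c − s). The retained difference is

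5 + 15·r·[λ(c − s) − λ(c)].

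**Case A: EVC does not affect the excluding test (s = 0).** The bracket is zero and the retained difference is 5.0 for every q and r.

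**Case B: EVC shifts the latent EON score by s = r·d** (0.200 for r = 0.6, 0.267 for r = 0.8).

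| Controls excluded | c | λ(c) | r | λ(c − s) | EVC excluded | Retained difference |
|---|---|---|---|---|---|---|
| 3% | −1.881 | 0.0701 | 0.6 | 0.0467 | 1.9% | 4.79 |
| 3% | −1.881 | 0.0701 | 0.8 | 0.0404 | 1.6% | 4.64 |
| 5% | −1.645 | 0.1086 | 0.6 | 0.0752 | 3.3% | 4.70 |
| 5% | −1.645 | 0.1086 | 0.8 | 0.0660 | 2.8% | 4.49 |
| 15% | −1.036 | 0.2743 | 0.6 | 0.2083 | 10.8% | 4.41 |
| 15% | −1.036 | 0.2743 | 0.8 | 0.1889 | 9.6% | 3.97 |

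Worked line (15%, r = 0.6): 5 + 15 × 0.6 × (0.2083 − 0.2743) = 5 − 0.59 = 4.41.

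Attenuation is thus about 4 to 10% with 3 to 5% of controls excluded, and about 12 to 21% with 15%.

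**Loss of infants.** Section 3.7 plans 40 per group with 20% loss, leaving 40 × 0.8 = 32. At 80% power and two-sided 5%, the detectable standardised difference is (1.960 + 0.842) × √(2/32) = 0.70. Assuming a further 5%, 10% or 20% excluded, 30.4, 28.8 or 25.6 per arm remain and it rises to 0.72, 0.74 or 0.78. The article does not say whether the 20% allowance covers these exclusions.

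**The case against.** The strongest case is that the rules may do little damage.

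- **The bias is conditional.** It arises only if EVC changes the excluding test. Section 2 predicts cognitive and linguistic gains and does not specifically predict changes in neurological signs or hearing. This stands, and Case A shows it. But the plan should not assume no effect on a measure it lists as an outcome, and even then infants are lost and the result describes only those who passed.
- **Exclusions may be few.** Sections 3.5 and 3.6 select a fairly low-risk cohort, so 15% may be too high. With 32 per arm the standard error of a Griffiths difference is 15 × √(2/32) = 3.75 points, well above a bias of 0.2 to 1.0 point. This also stands as to size. It does not justify the rule.
- **The rules may remove unrelated pathology.** An early hearing defect may predate treatment. But the tests are repeated to 24 months, and nothing confines the rule to pre-existing conditions.
- **Wording.** The meaning of a negative result is not defined, and the EON rule may reach only later visits. Under any of these readings, randomised infants are still removed on a post-allocation result.

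Three stronger inferences are tempting but unsupported.

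- A reader might say the comparison is conditioned on the outcome itself. The excluding tests are outcomes in the plan, but they are correlates of the scales being compared, not those scales.
- The hearing rule has no stated limit, so a reader might think it deletes HRV data. It sits among the secondary infant measures, and the primary analysis in Section 8.1 mentions no such exclusion.
- The criterion in Section 3.6 on "hyperbilirubinaemia requiring exchange transfusions during hospitalisation" might be read as a further removal after allocation. It is listed as an eligibility criterion, and nothing in the article applies it to the analysis of allocated infants.

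**Conclusion.** The concern holds for the two rules in Section 5.2.1 and for the developmental comparisons that depend on them. They restrict those comparisons to a subset defined after randomisation and treatment. Some loss of infants follows whenever a test is negative. Bias follows only if EVC affects neurological or hearing status, and in the model used it then runs towards no difference, attenuating a benefit or masking a harm.

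The illustrated range for a true 5-point benefit is 5.0 (no effect on the test) down to about 4.0 (15% of controls excluded, correlation 0.8). It rests entirely on assumed values and treats EON alone; no figure is offered for audiology. A scenario in which EVC acts only by preventing the excluded condition would reduce the difference to zero, but by construction, so it is not an estimate of size.

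The primary HRV outcome and its sample size are not affected on a natural reading.

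**What to change.** Replace the two exclusion sentences in Section 5.2.1 with text to this effect:

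1. Every randomised infant with outcome data is analysed in the allocated arm, whatever the EON or audiology result.
2. EON and audiology results are reported by arm as binary secondary outcomes, with the adverse category defined.
3. The subset with normal EON and audiology is used only for a labelled sensitivity analysis.

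This is a change of wording. It needs no new infants, visits or measurements. The downside is slightly greater outcome variance from keeping impaired infants, set against the infants retained and a comparison that respects allocation. How to score infants who cannot be tested is a separate choice of estimand, and this change does not depend on it.

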### 3.5. Inclusion Criteria

The inclusion criteria for the newborns will be: GA between 25 + 0 and 32 + 6 weeks at birth; Apgar score ≥ 7 at 10 min; birth weight between 3rd and 97th percentiles; birth cranial circumference greater than 10th percentile; periventricular leukomalacia (PVL) grade 1; intraventricular haemorrhage (IVH) grade 1–2; and hypoglycaemia, hyponatraemia, and hypocalcaemia are permitted, provided they are not persistent and severe. 

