### 3.9. Intervention

This intervention will start soon after birth, once the inclusion criteria are met, and will continue over 2 weeks during hospitalisation, minimising the effect of mother–infant separation in the NICU. In any case, participants will be excluded if they reach the inclusion criteria at more than 36 weeks of GA at test, thus when it’s presumed that they will not complete the two weeks of intervention. 

The EVC will take place in the hospital room while infants are in their individual incubators or open cribs. In the intervention group, mothers will be asked to speak and sing to their infants continuously over a 10 min period for each type of intervention (20 min in total). Mothers will be asked to talk in their native language and to sing familiar songs, while observing their infant’s reactions. The order of the two vocalisations, speaking and singing, will be reversed in the next intervention.

EVC will be performed by mothers three times per week for 2 weeks, more than 1 h after afternoon feeding. It will begin when the newborns are in an active sleep state, in calm awake state or in active awake state, but not in deep sleep or crying. 

The intervention will not begin during deep sleep state, in order to protect the infant sleep cycles and his stability [27]. The calm awake state is the most suitable for beginning early sensory interventions and interaction with the family, in stable preterm infants [70]. However, there is the need not to overwhelm the infant in this precious attentional state, where the brain expects sensory experience to grow and mature [20].

Preterm infants will be enrolled from 25 + 0 to 32 + 6 weeks of GA, following the established inclusion criteria.

Two fixed cameras will record the facial and upper torso movements of the mothers and infants. Mothers will be free to choose the content and style of their speech and singing, but will be asked to refrain from touching the infant, while maintaining eye contact with them. They will be told to place their face in front of the incubator opening so as to be as close as possible to the infant’s head. 

To improve adherence to the intervention protocol, concomitant medical procedures will not be permitted during the intervention. 

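### EVC may be given in any native language, but the dedicated language endpoints are in Italian and home language is neither a stratum nor a named covariate: avoidable variance and possible dilution, not bias

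*Protocol article*

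**What the plan says.** - **Delivery (3.9 Intervention).** "Mothers will be asked to talk in their native language and to sing familiar songs". The language is whatever the mother's happens to be.
- **Entry (3.5 and 3.6).** The infant criteria open with "The inclusion criteria for the newborns will be: GA between 25 + 0 and 32 + 6 weeks at birth" and continue with Apgar, growth, brain and metabolic conditions. For mothers: "The exclusion criteria for the mothers will be presence of depressive symptoms, drug abuse, and age below 18 years". Neither list mentions language.
- **Language endpoints (5.2.1 Infant's Measures).** "The Italian version of the MacArthur–Bates Communicative Development Inventory" is completed by parents at 12 and 24 months corrected age. In addition, "the expressive and receptive language test, Parole in Gioco [78], will be administered to infants by trained researchers at 24 months". The section gives every child a score on each questionnaire. It removes children with a negative neurological or audiological result but has no rule for home language.
- **Other language measure (5.2.1).** The Griffiths scales cover "locomotor, personal and social skills, hearing and language, eye and hand coordination, and performance". The language of testing is not stated.
- **Randomisation (3.8).** The sequence is "stratified by GA and gender".
- **Covariates (8.2 Secondary Outcomes).** "Confounding variables will be entered in the analysis (i.e., familiar socio-economical score, gestational age at birth"). Home language is not among them.

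**The concern.** The third hypothesis (section 2) is that early, regular exposure to speech in an interactive setting improves later cognitive and linguistic performance. The instruction on native language allows for mothers whose first language is not Italian. For their children, an Italian vocabulary score depends heavily on how much Italian they hear, and that has nothing to do with the arm they were assigned to.

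Two things follow:

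- **Variance.** A subgroup with a lower mean widens the score distribution in both arms, and nothing named in the analysis removes this.
- **Dilution.** If a benefit of EVC given in another language cannot show on an Italian instrument, the average difference between arms shrinks.

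Both act on endpoints that have no sample-size basis of their own, in a trial that expects about 64 children to remain (80 less 20%).

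**Working it through.** **The plan's own figure.** The only computed size, 29 per group in section 3.7, is for HRV. With two-sided alpha 0.025 and 80% power, HF power (difference 2, SD √((2.6² + 2.4²)/2) = 2.50) needs 2 × (2.241 + 0.842)² × 2.50² / 2² ≈ 30 per group, so 29 is reproduced to within one patient. It does not bear on the language endpoints, for which no calculation is given.

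**Inputs.**
- From the article: 40 per arm less 20% loss = 32 per arm.
- Assumed, because the article does not give them: share of homes where Italian is not spoken, p = 10% to 30%; mean deficit of their children on an Italian test, k = 0.5 to 1.5 SD, where 1 SD is the spread within a home-language group.

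**Formulas.** The SD of the mixed sample is √(1 + p(1−p)k²).
- (a) EVC's effect shows in every child: share of the standardised effect retained = 1 / √(1 + p(1−p)k²).
- (b) It cannot show in these children: share retained = (1−p) / √(1 + p(1−p)k²).

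| p | k | SD | (a) retained | (b) retained |
|---|---|---|---|---|
| 10% | 0.5 | 1.011 | 99% | 89% |
| 10% | 1.5 | 1.097 | 91% | 82% |
| 20% | 0.5 | 1.020 | 98% | 78% |
| 20% | 1.5 | 1.166 | 86% | 69% |
| 30% | 0.5 | 1.026 | 97% | 68% |
| 30% | 1.5 | 1.213 | 82% | 58% |

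Formula (b) uses the same SD in both arms. This is a simplification: if the effect is absent in these children, the gap between home-language groups is wider in the EVC arm.

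**In terms of power.** With 32 per arm and two-sided alpha 0.05, an effect of (1.960 + 0.842) × √(2/32) = 0.70 SD has 80% power when all homes speak Italian. Over the same grid, power becomes 79.1% to 63.6% under (a) and 70.3% to 36.5% under (b).

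**Chance imbalance is not a further harm.** Take p = 20% and k = 1.5.
- The SD of the arm difference in the share of such homes is √(2 × 0.2 × 0.8 / 32) = 0.10, which moves the arm difference by 0.10 × 1.5 = 0.15 SD.
- The standard error without the mixture is √(2/32) = 0.25. With it, it is √(2 × 1.36/32) = 0.292.
- Since 0.25² + 0.15² = 0.085 = 2 × 1.36/32, the imbalance is exactly the added variance. It should be counted once.

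**What adjustment recovers.** Conditioning on home language removes the p(1−p)k² term. Under (a) retention returns to about 100%. Under (b) it returns only to 1−p, that is 90%, 80% and 70% at shares of 10%, 20% and 30%.

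**The case against.** **Delivery in the native language and testing in Italian do not contradict each other.** In four Italian hospitals both can be reasonable, and an article may leave scoring detail to a fuller document. That stands as far as it goes. But the article does commit itself on strata and covariates, and its covariate list is worded as complete, so the omission of home language is part of the stated plan.

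**Language may be recorded already.** Section 4.1.2 mentions demographic data and a socio-economic questionnaire without listing their items. A reader might infer that language goes unrecorded; the article does not show this. It shows only that language is not named and not used.

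**The low scores are an expectation, not a documented fact.** The article gives no share of such homes and no deficit, and the language of Parole in Gioco is inferred from its title. This stands, and it is why the result is given as a range.

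**The largest losses need two unfavourable assumptions together.** The figure of 58% combines the highest share and deficit with no visible effect in these children. Section 2 speaks of linguistic performance in general, not vocabulary in one particular language, and six NICU sessions need not act only through the language then spoken. Scenario (a) is therefore at least as tenable as (b).

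**Other measures exist.** The Griffiths hearing and language sub-scale is given at 6, 12 and 24 months, and the 12-month inventory includes gestures. Both soften the point. With no test language stated for the Griffiths scales, they do not settle it.

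**Rank tests.** The Wilcoxon-Mann-Whitney test in 8.2 reduces the influence of a low tail but does not undo dilution.

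**Conclusion.** The concern holds as a matter of precision and possible dilution in the secondary language endpoints. Over the assumed ranges, the standardised effect keeps about 99% to 82% of its size if EVC's effect shows in every child, and about 89% to 58% if it cannot show on an Italian test in children from homes where Italian is not spoken. If few such families enrol, the harm is negligible.

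A reader might go further and infer that the language comparison is biased, or that an imbalance of such families could produce a false effect beyond the nominal error rate. The documents do not support that. Home language is fixed before randomisation, so the arms are balanced on it in expectation, and chance imbalance is already contained in the standard error. The primary HRV outcome is unaffected.

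**What to change.** 1. Record the mother's native language and the child's home language or languages at T0.
2. Add home language to the covariates in section 8.2 for the MacArthur-Bates and Parole in Gioco comparisons, with all randomised children kept in the main analysis. This needs a model that accepts covariates; the Wilcoxon-Mann-Whitney test named there does not take them.
3. Pre-specify a sensitivity analysis in children with Italian as a home language, defined from T0 data only.

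Making that subset the main analysis is not advised. It would shrink a small sample, and it would still include bilingual children whose mothers gave EVC in another language.

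The cost is one questionnaire item, one sentence in the analysis section and one model degree of freedom if home language is coded as Italian or not. Adjustment recovers the lost precision but not any dilution under scenario (b); the sensitivity analysis addresses that only in part.
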